## Abstract

**Background:**

Coronary artery disease (CAD) remains one of the leading causes of mortality and morbidity worldwide. As oxygen and nutrient supply to the myocardium significantly decrease during ischemic periods, important changes occur regarding myocardial intermediary energy metabolism. Metabolomics is an emerging field in systems biology, which quantifies metabolic changes in response to disease progression. This study aims to evaluate the diagnostic utility of plasma metabolomics-based biomarkers for determining the complexity and severity of CAD, as it is assessed via the SYNTAX score.

**Methods:**

Corlipid is a prospective, non-interventional cohort trial empowered to enroll 1065 patients with no previous coronary intervention history, who undergo coronary angiography in University Hospital AHEPA, Thessaloniki. Venous blood samples are collected before coronary angiography. State-of the-art analytical methods are performed to calculate the serum levels of novel biomarkers: ceramides, acyl-carnitines, fatty acids, and proteins such as galectin-3, adiponectin, and the ratio of apolipoprotein B/apolipoprotein A1. Furthermore, all patients will be categorized based on the indication for coronary angiography (acute coronary syndrome, chronic coronary syndrome, preoperative coronary angiography) and on the severity of CAD using the SYNTAX score. Follow-up of 12 months after enrollment will be performed to record the occurrence of major adverse cardiovascular events. A risk prediction algorithm will be developed by combining clinical characteristics with established and novel biomarkers to identify patients at high risk for complex CAD based on their metabolite signatures. The first patient was enrolled in July 2019 and completion of enrollment is expected until May 2021.

**Discussion:**

CorLipid is an ongoing trial aiming to investigate the correlation between metabolic profile and complexity of coronary artery disease in a cohort of patients undergoing coronary angiography with the potential to suggest a decision-making tool with high discriminative power for patients with CAD. To our knowledge, Corlipid is the first study aspiring to create an integrative metabolomic biomarkers-based algorithm by combining metabolites from multiple classes, involved in a wide range of pathways with well-established biochemical markers.

*Trial registration* CorLipid trial registration: ClinicalTrials.gov number: NCT04580173. Registered 8 October 2020—Retrospectively registered, https://clinicaltrials.gov/ct2/show/NCT04580173.

## Background

Atherosclerosis is a pathological process strongly correlated with metabolic disorders of lipid oxidation stress [1]. Its consequent inflammatory alterations on the endothelium could lead to coronary artery disease (CAD), including stable and acute coronary syndrome. Risk factors associated with the initiation and the propagation of the atherosclerotic process have been identified as a result of the intense investigation over the last decades in this scientific field. Apart from traditional risk factors, such as age, sex, race, smoking, LDL and HDL cholesterol, systolic blood pressure, family history of premature myocardial infarction, diabetes mellitus and triglycerides, there are multiple studies integrating novel biomarkers, such as a genetic ones, cardiac troponin-T, high sensitivity C-reactive protein, apolipoprotein B/ apolipoprotein A-1 ratio, homocysteine or coronary artery calcium in CAD risk stratification [2, 3].

However, despite the remarkable progress in diagnosing and treating CAD during the last decade, it remains the leading cause of morbidity and mortality worldwide [4], while prognostic prediction remains challenging in this cohort of patients. This could be attributed to a lack of effective diagnostic methods for CAD in its early stages, and a poor understanding of its pathophysiology. Thus, further studies are still warranted to increase our understanding of the complex pathophysiological mechanisms underlying CAD and to shed light on novel CAD risk parameters.

Recently emerging scientific evidence supports that cardiac metabolism disturbances indicate high probability of cardiovascular disease [5]. Hence, metabolomics, one of the newest and most rapidly evolving omics techniques, could be employed as a targeted tool for determining cardiac metabolism perturbation [6, 7]. According to the American Heart Association, cardiovascular metabolomics is a promising field able to provide detailed metabolic profiling of biospecimens and investigate both the intrinsic and extrinsic factors that contribute to CAD risk [8]. More specifically, multiple studies revealed that various metabolites such as BCAAs (branched-chain amino acids), specific unsaturated lipid species [8], trimethylamine-N-oxide [9], choline [10, 11], cysteine, N-acetylalanine and theophylline [12] are linked with an advanced cardiometabolic risk profile derived through metabolomics-based analysis using Liquid Chromatography-Mass Spectrometry or Nuclear Magnetic Resonance Spectroscopy. Furthermore, there are also data suggesting that other already established biochemical markers, such as cholesterol and triglycerides, have been strongly associated with CAD pathogenesis [6]. Therefore, their clinical importance in prediction and risk stratification of cardiovascular events should be thoroughly evaluated.

The rationale of this real-world observational study is by measuring metabolic profiles to expand our knowledge on the biochemical process of atherogenesis and to identify clinically significant metabolic biomarkers associated with the pathogenesis and the prognosis of CAD. Previous studies have already been conducted trying to establish potential correlations between metabolic profiling and CAD [11–14]. However, to the best of our knowledge, this is the first study aiming to associate the severity and the complexity of CAD, as assessed by the SYNTAX score [15] with patients’ metabolic profile. This study's ultimate goal is to suggest a clinical tool of personalized medicine based on the patients' metabolic fingerprint to distinguish the patients at high risk for adverse cardiovascular events.

## Methods

### Study design and population

CORLIPID (ClinicalTrials.gov Identifier: NCT04580173) is an investigator-initiated, prospective, non-interventional cohort trial involving patients undergoing coronary angiography.

Every trial procedure was conducted following the principles set by the declaration of Helsinki and the International Conference on Harmonization Guidelines for Good Clinical Practice [16]. The Scientific Committee of AHEPA University Hospital has approved the study protocol (reference number 12/13-06-2019). Every patient attested informed consent before being enrolled in our study.

A total of 1065 patients presenting to AHEPA University Hospital, who undergo scheduled or emergency coronary angiography, will be enrolled in the study. Patients with a history of previous Coronary Artery Bypass Graft or Percutaneous Coronary Intervention are excluded, as it is not possible to calculate the SYNTAX score for these patients. Detailed eligibility criteria are described in Table 1.

**Table 1 Tab1:** Selection criteria for the enrollment in the CorLipid study

Inclusion criteria	Exclusion criteria
Patients undergoing coronary angiography without medical history of coronary artery disease Age > 18 years old Informed consent for study participation	Medical history of prior percutaneous coronary intervention Medical history of prior coronary artery bypass grafting Cardiopulmonary arrest Severe concomitant disease with a life expectancy less than 1 year

The following clinical characteristics were recorded for each patient: demographics, medical history and medication, as well as serum biochemical markers obtained on the enrollment day. Furthermore, patients were categorized into: (1) patients without CAD symptoms (undergoing preoperative coronary angiography prior to cardiac valve surgery), (2) patients with stable angina, (3) patients with acute coronary syndrome (unstable angina, non-ST elevation myocardial infarction (NSTEMI) and ST-elevation myocardial infarction (STEMI)).

In addition, coronary angiographic images of every patient were evaluated by two experienced independent interventional cardiologists blinded to the clinical aspects and the outcome of the patients and the SYNTAX score was calculated. Based on SYNTAX score, patients were classified into: (1) patients with low SYNTAX score (0–22), (2) patients with intermediate SYNTAX score (23–32) and (3) patients with high SYNTAX score (> 32) [15].

Venous blood sample was collected from all participants prior to coronary angiography. The blood collection vials were placed for incubation for 30 min. Immediately after centrifugation at 4000 rpm for 10 min at room temperature, the serum samples were stored at − 80 °C.

Telephone follow-up will be performed on the 12^th^ month after study entrance for each patient to document the occurrence of CAD symptoms, major adverse cardiovascular and cerebrovascular events (MACCE-cardiovascular death, acute myocardial infarction, need for revascularization, stroke episode) or bleeding complications.

### Biochemical analysis-metabolomics

Metabolomics-based analysis using Gas Chromatography tandem Mass Spectrometry (GC–MS) as well as targeted methods based on Liquid Chromatography tandem Mass Spectrometry (LC–MS) and Gas Chromatography with Flame Ionization Detector (GC-FID) will be performed. The untargeted approach will be used as it offers the advantages of novel biomarkers discovery from a wide range of compounds. The quantification of four ceramide species (C18:0/16:0, C18:0/18:0, C18:0/24:0 and C18:0/24:1) with their respective ratios and of fifteen short-, medium- and long chain acylcarnitines in serum CAD patients will be achieved with targeted methods by applying a developed RPLC and HILIC LC –MS/MS method, respectively. The composition of total fatty acids will be quantitatively measured in patients’ serum samples using a developed GC-FID based method. In addition, protein markers associated with CAD, namely Galectin-3, adiponectin, NGAL and ApoB/ ApoΑ-Ι will be measured by enzyme-linked immunosorbent assay (ELISA) in serum patients’ samples in order to enhance the predictive value of the CorLipid panel.

### Statistical considerations

#### Sample size estimation

Sample size estimation for studies utilizing metabolomic data in various degrees is not straightforward as effect sizes are not readily established in this very active area of research. The primary endpoint of the study is to discover potential correlations of clinical types of Coronary Artery Disease with patients' metabolic profile. Syntax score as a descriptor of CAD complexity could be probably correlated with an array of known and novel small molecule biomarkers to determine if the varying level of CAD complexity is related to metabolism.

Targeted analyses on concentrations of known molecules, such as Ceramides, Galectin-3, Adiponectin, NGal etc. will be the majority of the metabolic profile analyses conducted and we intent to explore potential correlations of them with the Syntax score. This multiparametric approach hinders a more accurate estimation of an effect size, as there is a multitude of factors at play. Thus, using a pilot study of 100 patients, we performed a linear multiple regression random model to establish an effect size for a direct effect on the SYNTAX score from various parameters. In this pilot study we chose 10 predictors (concentrations of current and potential biomarkers and categorical parameters) as in the expanded study we will aim to choose smaller more concise models with less than 10 predictors of better biological interpretations.

Using the G*Power tool [17] and a calculated effect based on a regression model R^2^ of 0.370, an effect size of H1 p^2^ 0.30 was yielded. We expect other factors, not explicitly measured by this study, to also independently influence CAD complexity as measured by Syntax score, so we arbitrary assume a Η0 ρ^2^ of 0.20. So for an A of 0.01 and a Power of 0.95 a sample size of 1014 is sufficient. This initial sample size will be increased by 5%, as some study participants might be lost to follow-up. Hence, we aim for a total of 1065 patients.

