### Statistical analysis

Normally distributed data will be analyzed using parametrical tests, such as Student *t*-test and for non-normally distributed data nonparametric test such are Mann–Whitney and multiparametric Kruscal-Wallis H test will be utilized, as indicated by the Kolmogorov-Smirnoff Test for normality. Categorical variables will be compared using the χ^2^ test. Continuous data will be presented as mean ± SD, whereas categorical variables will be displayed as counts and percentages. Univariable, multivariable and correlations analysis will be carried out to clarify independent predictors of various CAD characteristics, biochemical measurements and associations with SYNTAX score, metabolic biomarkers individually as well as follow up MACCE.

Linear and logistic regression, using stratified bootstrapping if needed to account for potential non-parametric data, will be used to identify independent predictors of CAD characteristics and Syntax Score. Receiver operating characteristic (ROC) curve analysis -and derived area under the curve (AUC) -will be utilized when appropriate. Cox regression analyses and Kaplan–Meier survival will be calculated for the 1 year follow-up for Syntax score groups and to check the validity of potential predictive models that will emerge, with the difference between different patient sub-groups analyzed by the log-rank test. Patients that are lost to follow-up will be censored at their last study encounter. The level of statistical significance will be considered at a = 0.05 and every statistical test will be performed via SPSS v. 26.

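### The 95% power belongs to a whole-model R² test against a null of 0.20 whose stated reason does not support it; it does not carry over to a conclusion about metabolites

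*Protocol article*

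**What the plan says.** The Sample size estimation section of the protocol article takes its effect size from a pilot: "using a pilot study of 100 patients", it reports that "we performed a linear multiple regression random model to establish an effect size for a direct effect on the SYNTAX score from various parameters". On the predictors it says "we chose 10 predictors (concentrations of current and potential biomarkers and categorical parameters", so biomarkers and categorical factors sit in one model.

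It then used G*Power with "a calculated effect based on a regression model R^2^ of 0.370, an effect size of H1 p^2^ 0.30 was yielded". The null value is explained by other factors "not explicitly measured by this study, to also independently influence CAD complexity as measured by Syntax score, so we arbitrary assume" it; in full, "so we arbitrary assume a Η0 ρ^2^ of 0.20". With alpha 0.01 it concludes that for "a Power of 0.95 a sample size of 1014 is sufficient", and adds 5% for loss to follow-up to reach 1065.

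The Statistical analysis section lists group comparisons, correlations, linear and logistic regression for independent predictors of CAD characteristics and SYNTAX score, ROC curves, Cox regression and Kaplan–Meier curves. On the error rate it says "The level of statistical significance will be considered at a = 0.05". It mentions neither a test at 0.01 nor a comparison of R² with 0.20.

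The Endpoints section gives the primary aim as a risk model that combines clinical characteristics with established and novel biomarkers, to find patients at high risk of CAD, and above all of complex CAD, from their metabolite signatures.

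**The concern.** Three things do not fit together.

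- **The reason for the null.** In this test ρ² is the share of SYNTAX variance explained by the predictors in the model. Influences that the study does not measure lie in 1 − ρ². They give no ground for supposing that the measured predictors explain 20% under the null. The article neither reports an R² for clinical variables alone nor says that 0.20 stands for one.
- **The link to the analysis.** The size was set at alpha 0.01 for a test of ρ² against 0.20. The article's own analysis section works at 0.05 and names no such test.
- **What the test can show.** R² of a pooled model does not separate the metabolite contribution from that of established markers and categorical factors. If the latter alone explained 30% of the variance, the sized test would succeed with no metabolite contribution.

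At stake is how the 95% is read. It is the only justification given for the size of a metabolomics study, and a reader will naturally take it as power for a finding about metabolites.

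**Working it through.** **Inputs** (Sample size estimation): pilot n = 100, 10 predictors, pilot R² = 0.370, H1 ρ² = 0.30, H0 ρ² = 0.20, alpha 0.01 (sidedness not stated), power 0.95, N = 1014, plus 5%. From Statistical analysis: alpha 0.05.

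**1. Reproducing 1014.** With random regressors, the exact distribution of the sample R² is a mixture: J ~ NegBin((N−1)/2, 1−ρ²), and R² given J ~ Beta(p/2 + J, (N−p−1)/2), with p = 10.

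| Test of 0.20 vs 0.30, power 0.95 | N | Power at 1014 |
|---|---|---|
| Two-sided, alpha 0.01 | 1014 | 0.950 |
| One-sided, alpha 0.01 | 900 | 0.971 |
| Two-sided, alpha 0.05 | 745 | 0.988 |

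The plan's figure is therefore the two-sided test at alpha 0.01 (power 0.9498 at 1013, 0.9500 at 1014). Rejecting upward needs an observed R² of at least 0.267. The increase checks too: 1014 × 1.05 = 1064.7, rounded to 1065.

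**2. Where 0.30 comes from.** Adjusted pilot R² = 1 − (1 − 0.370) × 99/89 = 0.299. The article does not name this adjustment, but the match is close.

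**3. How much rests on 0.20.** Two-sided, alpha 0.01, power 0.95, H1 = 0.30, 10 predictors:

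| H0 ρ² | 0 | 0.10 | 0.15 | 0.18 | 0.20 | 0.22 | 0.25 |
|---|---|---|---|---|---|---|---|
| N | 98 | 241 | 441 | 698 | 1014 | 1597 | 4132 |

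Moving the null by 0.05 either way changes N from 1014 to 441 or 4132. The sample size is largely set by a value with no valid rationale.

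**4. What 1014 patients can do for the metabolites.** The matching test is a nested F-test of q biomarkers added to a base model, with f² = ΔR² / (1 − R² of the full model) and noncentrality f² × N. The documents give no base-model R², so a full-model R² of 0.30 is an assumption, taken from the article's H1. At N = 1014, alpha 0.01 and power 0.95:

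- q = 5: f² = 0.0256, so ΔR² = 0.0256 × 0.70 = 0.018.
- q = 10: f² = 0.0312, so ΔR² = 0.0312 × 0.70 = 0.022.

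At alpha 0.05 the detectable increment for q = 5 is 0.014. For a true increment of 0.01 with q = 5, power is 0.67 at alpha 0.01 and 0.85 at alpha 0.05.

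**The case against.** Several points on the other side are sound.

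- **The analysis might still be planned.** Linear regression on the SYNTAX score is in the Statistical analysis section, so the model family matches the sizing. A reader might infer that the powered test will never be run. The documents do not support that: a full protocol or SAP could name it. What stands is that the article gives two alphas and does not connect its 95% to any analysis it describes.
- **The alpha mismatch is conservative.** Sizing at 0.01 and testing at 0.05 raises the power of the same test to 0.988. The conflict needs reconciling, but it costs no power.
- **The null is disclosed as arbitrary and is demanding.** Against ρ² = 0 the same alternative needs only 98 patients. Disclosure does not repair the reasoning, but it does mean that nothing is hidden.
- **The pilot was handled with some care.** H1 was already reduced from 0.370 to 0.30. The pilot's exact 95% interval for ρ² is 0.14 to 0.46, and a reader might count its covering 0.20 as a defect. It is not: a pilot of 100 is not meant to reject the null. Power does fall if ρ² is smaller (66% at 0.27, alpha 0.01), as it does in any design.
- **Added value is not stated as a formal hypothesis.** The primary aim is a combined model, for which overall R² is a defensible target. But the same sentence ties identification to metabolite signatures, and Sample size estimation asks whether CAD complexity is related to metabolism. A pooled R² answers neither.

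A reader might also infer that 1065 patients are too few. Nothing here shows that; the detectable increments suggest reasonable sensitivity.

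**Conclusion.** The point holds as a should-fix. The 1014 is correct for a two-sided, alpha 0.01 test of whole-model ρ² = 0.20 against 0.30 with 10 pooled predictors. The reason given for 0.20 is wrong as written, the two sections disagree on alpha, and the quantity that was powered cannot isolate the metabolites. The 95% should not be read as power for a metabolite conclusion.

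The error is in what the number supports, not in its calculation. Recast for added value, 1014 patients give 95% power at alpha 0.01 for an R² increment of about 0.018 (5 biomarkers) to 0.022 (10 biomarkers). Those figures assume a full-model R² of 0.30 and a biomarker set fixed before the analysis. Whether increments of that size are realistic or useful cannot be judged from the documents.

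**What to change.** Keep 1065 patients, and change the text as follows.

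1. In Sample size estimation, drop the argument from unmeasured factors.
2. State the powered hypothesis as: a targeted biomarker set, fixed before the analysis, adds no explained variance in the SYNTAX score beyond a pre-specified model of clinical variables and established markers. Test it with a nested F (likelihood-ratio) test.
3. Name that test in Statistical analysis, with the same alpha in both sections.
4. Keep metabolites from the untargeted work, or chosen by data-driven model reduction, exploratory. The alpha and power of the nested test do not hold after selection, and the article plans both untargeted discovery and smaller chosen models.
5. Replace the 95% headline with the detectable increment and its assumption: at alpha 0.01, about 0.018 for 5 biomarkers to 0.022 for 10, with full-model R² 0.30.

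The cost is wording, one extra model comparison, and the loss of a simple 95% claim. No patients or assays are added. A linear R² increment does not replace the logistic and ROC analyses aimed at identifying high-risk patients, which should stay.

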### Statistical analysis

Normally distributed data will be analyzed using parametrical tests, such as Student *t*-test and for non-normally distributed data nonparametric test such are Mann–Whitney and multiparametric Kruscal-Wallis H test will be utilized, as indicated by the Kolmogorov-Smirnoff Test for normality. Categorical variables will be compared using the χ^2^ test. Continuous data will be presented as mean ± SD, whereas categorical variables will be displayed as counts and percentages. Univariable, multivariable and correlations analysis will be carried out to clarify independent predictors of various CAD characteristics, biochemical measurements and associations with SYNTAX score, metabolic biomarkers individually as well as follow up MACCE.

Linear and logistic regression, using stratified bootstrapping if needed to account for potential non-parametric data, will be used to identify independent predictors of CAD characteristics and Syntax Score. Receiver operating characteristic (ROC) curve analysis -and derived area under the curve (AUC) -will be utilized when appropriate. Cox regression analyses and Kaplan–Meier survival will be calculated for the 1 year follow-up for Syntax score groups and to check the validity of potential predictive models that will emerge, with the difference between different patient sub-groups analyzed by the log-rank test. Patients that are lost to follow-up will be censored at their last study encounter. The level of statistical significance will be considered at a = 0.05 and every statistical test will be performed via SPSS v. 26.

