### Patient recruitment and baseline characteristics

From o till September 2020, a total of 596 patients were enrolled in the study. Mean age was 63.71 (SD ± 12.68) years. 266 patients (44.63%) presented with acute coronary syndrome, of whom 106 patients were diagnosed with STEMI, 99 patients were diagnosed with NSTEMI and 66 patients suffered from unstable angina. 330 patients presented with Chronic Coronary Syndromes. Hypertension was found in 56.5% of patients. About 28.7% were diabetics, while dyslipidemia was observed in 38.4%. Smoking was reported by 41.5% of patients. During the aforementioned recruitment period the mean SYNTAX score of the patients was 11.5. The baseline characteristics of study participants are shown in Table 2. Completion of enrollment is expected until May 2021.

**Table 2 Tab2:** Baseline characteristics of study participants

Βaseline characteristics	Ν	%
Male gender	438	73.5
*Age groups*		
65 <	318	53.5
65 >	277	46.5
Hypertension	337	56.5
Diabetes mellitus	171	28.7
Dyslipidemia	229	38.4
Acute coronary syndrome	266	44.5
NSTEMI	99	16.6
STEMI	106	17.8
*Angina*		
Unstable	66	11.1
Stable	96	16.1
Use of statins	286	47.5
*SYNTAX score groups*		
0–22	490	82.2
23–32	72	12.1
> 32	34	5.7

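### Choosing Student's t or a rank test by a normality test does not protect the 0.05 level if spreads differ across the unbalanced SYNTAX classes, and mean ± SD does not match a rank p-value (minor)

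*Protocol article*

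**What the plan says.** The Statistical analysis section of the protocol article sets three rules.

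- **Choice of test.** "Normally distributed data will be analyzed using parametrical tests, such as Student" t-test. By contrast, "for non-normally distributed data nonparametric test such are Mann–Whitney and multiparametric Kruscal-Wallis H test will be utilized". The choice is made "as indicated by the Kolmogorov-Smirnoff Test for normality". No check of equal spread and no unequal-variance test is named.
- **Summary.** "Continuous data will be presented as mean ± SD, whereas categorical variables will be displayed as counts and percentages". No exception is made for variables tested on ranks.
- **Level.** "The level of statistical significance will be considered at a = 0.05".

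Study design and population defines three SYNTAX classes (0–22, 23–32, above 32). Table 2 gives their sizes among the first 596 patients as 490, 72 and 34. The acute/chronic split is close to even: "266 patients (44.63%) presented with acute coronary syndrome", and the other 330 had chronic syndromes. The Statistical analysis section does not say which groups the t and rank tests compare. It also plans linear and logistic regression, with bootstrapping if needed, and ROC analysis. Endpoints makes a risk prediction model the primary aim.

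**The concern.** Student's t-test in its usual form pools the variance. The reference distributions of Mann–Whitney and Kruskal–Wallis assume that the groups have the same shape and spread under the null. With groups of similar size a difference in spread does little harm. With 82.2/12.1/5.7% it can do a lot, because the pooled variance is almost wholly that of the large low-SYNTAX class, while the uncertainty of the contrast comes mostly from the small class. A normality test does not look at this.

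What happens depends on direction. If the small, high-SYNTAX class is more variable, the test rejects too often. If it is less variable, real differences are missed. Either way the stated 0.05 is not the actual rate for a single test, before any multiplicity.

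Separately, a variable that the plan itself classes as non-normal gets a p-value from ranks but is displayed as mean ± SD. The reader then sees a contrast of means beside a p-value that does not test means.

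**Working it through.** **Inputs.** Table 2: 490 + 72 + 34 = 596, or 82.2%, 12.1% and 5.7%. At the planned 1065: 1065 × 0.822 = 875, 1065 × 0.121 = 129, 1065 × 0.057 = 61. This assumes that the shares of the first 596 carry over. Level 0.05, taken as two-sided because sidedness is not stated. The article gives no marker SDs, so the SD ratio r (small class over large class) is an assumption and is shown over a range.

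**Pooled t-test, near-normal marker, equal means.** Give the large class (n₁ = 875) SD 1 and the small class (n₂ = 61) SD r.

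- Pooled variance: sp² = [(n₁−1) + (n₂−1)r²] / (n₁+n₂−2)
- Squared standard error used: sp²(1/n₁ + 1/n₂)
- True squared standard error: 1/n₁ + r²/n₂
- k = square root of used/true; rejection rate ≈ 2Φ(−1.96k)

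At r = 1.5:

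- sp² = (874 + 60 × 2.25)/934 = 1009/934 = 1.080
- used = 1.0803 × 0.017536 = 0.01894
- true = 0.001143 + 0.036885 = 0.03803
- k = √(0.01894/0.03803) = 0.706
- 2Φ(−1.383) = 0.167

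| r | k | Formula | Simulated pooled t | Simulated Welch |
|---|---|---|---|---|
| 0.67 | 1.411 | 0.6% | about 0.7% | 4–6% |
| 1.0 | 1.000 | 5.0% | about 5% | 4–6% |
| 1.25 | 0.824 | 10.6% | 10–11% | 4–6% |
| 1.5 | 0.706 | 16.7% | about 16% | 4–6% |
| 2.0 | 0.560 | 27.2% | about 27% | 4–6% |

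The row r = 1.0 reproduces the plan's own level.

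**Other splits.** The rate depends on the balance of the groups and hardly on the total, so more patients do not cure it. Simulated pooled t at r = 1.5 and 2: 17% and 28% for 490 versus 34, 13% and 19% for 490 versus 106, 13% and 20% for 876 versus 189. Kruskal–Wallis on 490/72/34 rejects 11% with SDs 1/1.5/1.5, 12% with 1/1.5/2, 16% with 1/2/2, and 1% with 1/0.67/0.5.

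**Does the normality test help?** Applied within each group of 490 and 34, it passes normal data in about 91% of runs at every SD ratio tried (0.95² = 0.90 is expected), so it is blind to spread. The whole procedure then rejects 17% at r = 1.5 and 26% at r = 2. Applied to the pooled sample at 875 versus 61, it flags 4–5% of data sets at r = 1.25–1.5 and 26% at r = 2, and the whole procedure rejects 9.8%, 16.9% and 22.7% at r = 1.25, 1.5 and 2. The article does not say which application is meant. The conclusion is the same.

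**Skewed markers.** For log-normal data (log-SD 0.4 in the large class, 0.4 to 0.8 in the small one, 936 patients) the normality test flags every data set, so the t-test is never reached. With equal medians, Mann–Whitney rejects about 10% at log-SD 0.6 and 13% at 0.8 in the small class. Welch on the log scale stays at about 5%.

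**Acute versus chronic, 266 versus 330.** At SD ratios 0.5 to 2 on normal and heavy-tailed data, pooled t rejects 3.6–6.9% and Mann–Whitney about 5–7%. There is almost no effect.

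**Summary statistic.** No arithmetic is needed. The rule for non-normal data gives a rank test, and the rule "Continuous data will be presented as mean ± SD" has no exception, so the two rules conflict for exactly those variables.

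**The case against.** The best case for the plan is that this touches little of what matters. The t and rank tests are not tied to the SYNTAX classes, and a t-test cannot compare three classes, so high versus low SYNTAX is a contrast that the reader supplies. The sample size is for multiple regression and the primary aim is a prediction model. The group contrast that Endpoints does name, acute versus chronic, is nearly balanced. The wording (such as) does not exclude Welch, and a condensed article may leave test variants and medians to a fuller document. All of this stands, and it limits the point to supporting univariate comparisons. It does not remove it: the article states the selection rule and the summary rule outright, and Student's is the only parametric test it names.

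Three stronger readings are tempting and are not supported.

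- **That unequal spread will produce false marker differences in this study.** That needs the small class to be the more variable one, and no marker SD is given. In the opposite case the test is too conservative. The 16–27% figures also apply only to near-normal markers; skewed ones go to the milder rank test.
- **That a rank test rejecting skewed markers with equal means is in error.** With equal means and unequal log-SDs the medians truly differ, and Welch on the log scale would also reject often. This shows that means and ranks answer different questions; it is not an error rate.
- **That mean ± SD must run below zero for SYNTAX.** The article reports "During the aforementioned recruitment period the mean SYNTAX score of the patients was 11.5" but no SD, and deriving one needs assumed class means.

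**Conclusion.** The point holds in limited form and is minor. As written, the method is chosen by a property (shape) that does not protect the level, and the summary does not match the test for variables tested on ranks. The second part needs no assumption.

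The first part is conditional on three things: the tests being used across the SYNTAX classes, the Table 2 shares holding at 1065, and spreads differing. If they do, the actual level at 875 versus 61 runs from about 0.7% (SD ratio 0.67) to about 27% (ratio 2.0) for near-normal markers under pooled t. For skewed markers under Mann–Whitney at equal medians it is about 10–13%. With equal spread the level is correct. The acute/chronic contrast and the primary regression and ROC analyses are hardly affected.

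**What to change.** In the Statistical analysis section:

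1. Replace selection by the normality test with one method per variable, set in advance.
2. Use Welch's t-test for two groups and Welch's ANOVA for three in place of Student's t, on the log scale for positive, skewed concentrations.
3. Where a two-group rank test is kept, use Brunner–Munzel. It held 4–6% at SD ratios 0.5 to 2 for 490 versus 34 and 490 versus 106. Check that SPSS v. 26, the software named for every test, offers it; if not, amend that sentence too.
4. Report geometric means, with ratios and 95% confidence intervals, for log-analysed markers, and median (interquartile range) for rank-tested or otherwise skewed variables, SYNTAX included.

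The cost is a few sentences, with no new data or patients. Power at equal spread falls very little: 85.3% for Student against 84.5% for Welch in simulation at 875 versus 61, with an assumed true difference of 0.4 SD. At SD ratio 0.67 Welch gains, 99.3% against 94.5%. Where the small class is the more variable one, intervals become wider, which reflects the real uncertainty.
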